## Abstract

**Background:**

The gut microbiota has been implicated in the onset and progression of Rheumatoid Arthritis (RA). It has been proposed that gut dysbiosis impairs gut barrier function, leading to alterations in mucosal integrity and immunity. This disruption allows bacterial translocation, contributing to the perpetuation of the inflammatory process. Since diet is recognised as a key environmental factor influencing the gut microbiota, nutritional interventions targeting RA activity are currently being explored. This study aims to investigate whether a dietary intervention based on a typical Mediterranean Diet enriched with fermented foods (MedDiet +) can impact the gut microbiota, intestinal permeability, and RA-related outcomes.

**Methods:**

One hundred RA patients are being recruited at Unidade Local de Saúde (ULS) Santa Maria in Lisbon, Portugal, and randomly assigned to either the intervention (MedDiet +) or the control group. The 12-week nutritional intervention includes a personalised dietary plan following the MedDiet + pattern, along with educational resources, food basket deliveries, and clinical culinary workshops, all developed and monitored weekly by registered dietitians. The control group receives standardised general healthy diet recommendations at baseline. The intervention's effects will be assessed by evaluating disease activity, functional status, quality of life, intestinal permeability, endotoxemia, inflammatory biomarkers, intestinal and oral microbiota, serum proteomics, and serum glycome profile characterisation.

**Discussion:**

We anticipate obtaining integrative insights into the interplay between diet, the gut, and RA, while also exploring the underlying mechanisms driving these changes. This study, conducted by a multidisciplinary research team of registered dietitians, rheumatologists, biologists, and immunologists, aims to bridge the current gap between nutrition-related knowledge and RA.

**Trial registration:**

Registered in ClinicalTrials.gov (NCT06758817; date of registry: January 6th 2025).

**Supplementary Information:**

The online version contains supplementary material available at 10.1186/s12937-025-01089-6.

## Introduction

Rheumatoid Arthritis (RA) is a chronic immune-mediated disease characterised by inflammation of the synovial tissue of joints, which leads to progressive destruction of cartilage and bone, and ultimately impacts patients' functional capacity and quality of life [1, 2]. While genetic susceptibility is well-documented as a contributing factor in RA development, environmental factors are increasingly recognised to be involved in the onset and progression of the disease [3].

An imbalance in the composition and function of the gut microbiota, referred to as gut dysbiosis, has been identified as a key modulator of immune responses and an important factor in the development of immune-mediated disorders [4, 5]. The mechanism whereby this may occur is related to the influence of dysbiosis in disrupting the integrity and function of the intestinal barrier, as well as mucosal immunity [6, 7]. Increased intestinal permeability facilitates translocation of bacteria and their components, leading to endotoxemia, results in low-grade systemic inflammation, increased inflammatory biomarkers, and can thus contribute to the inflammatory process [7, 8]. The increased inflammation may take place not only at the epithelial level but also systemically, affecting the joints and linking intestinal dysfunction and rheumatic disorders [9]. Although dysbiosis and gut barrier dysfunction have been described in RA [10, 11], the specific ways in which diet could influence the relationship between gut integrity and systemic inflammation in RA remain to be fully elucidated.

Over the past few years, evidence has shown that patients with RA exhibit significant changes in their intestinal microbiota composition compared to healthy controls, including a marked decrease in α-diversity [12]. In light of these findings, the therapeutic modulation of the gut microbiota is being increasingly explored in RA, with a particular interest in dietary interventions, as diet is recognised as one of the main environmental factors influencing intestinal microbiota [13]. Both microbial and dietary metabolites have immunomodulatory properties that might be beneficial and could help manage immune-mediated and inflammatory disorders, including RA [14]. The relevance of whole dietary patterns, rather than individual nutrients, is progressively being addressed in RA, with an emphasis on the Mediterranean Diet (MedDiet) [6, 15, 16]. In this context, our group has recently shown that higher adherence to the MedDiet is associated with lower disease activity, lower impact of disease, and lower functional disability in RA patients [17].

It is also worth noting that the implications of the microbiota in RA go beyond the gut. Perturbations in oral microbiota have been found in individuals at high risk for RA [18], and in patients already diagnosed with RA [19]. Of interest, epidemiological evidence has linked periodontitis with RA, and it is hypothesised that certain perioral bacteria may contribute to the shift from health to disease by making post-translational modifications of proteins, such as citrullination, and thus provoking autoantibody production [20, 21]. In line with this, post-translational modification by glycosylation of circulating antibodies has been also described to precede the onset of other immune-mediated diseases such Inflammatory Bowel Disease [22]. This adds to the possible mechanisms contributing to RA onset and may also play a role in RA progression. Therefore, both oral and gut microbiota should be explored in integrative study designs.

Overall, when considering nutritional interventions in RA, the promotion of a symbiotic microbiota and its consequent influence on intestinal barrier integrity, endotoxemia and inflammatory biomarkers represents a plausible mechanism linking diet to improved clinical outcomes in these patients. Accordingly, this trial has been designed to investigate the triad of nutrition, intestinal microbiota, and RA by assessing the effects of a nutritional intervention specifically designed to enhance gut microbiota diversity.

## Methods

### Study design, setting and aims

This is a single-centre randomised controlled trial, coordinated and implemented at Faculdade de Medicina, Universidade de Lisboa (FMUL), Gulbenkian Institute for Molecular Medicine (GIMM) and Unidade Local de Saúde (ULS) Santa Maria, Centro Académico de Medicina de Lisboa (CAML), Lisbon, Portugal. This trial is registered in ClinicalTrials.gov (NCT06758817; date of registry: January 6th 2025). This trial was approved by the ethics committee of CAML (Ref. Nº114/22).

We aim to investigate whether a nutritional intervention based on a MedDiet enriched with fermented foods (MedDiet +) may influence disease activity, functional status, quality of life, intestinal permeability, endotoxemia, inflammatory biomarkers, intestinal and oral microbiota, serum proteomics and serum glycome.

The first participant was enrolled in July 2023, and data collection is anticipated to conclude by the end of 2025. Currently, the effect of the MedDiet on the Disease Activity Score in 28 joints (DAS28) of RA patients is not yet known, making it unfeasible to conduct a formal sample size calculation. Considering the number of potentially eligible RA patients treated at the Rheumatology Department at ULS Santa Maria, our recruitment capacity, available funding, and the size of recent published studies in this area, a convenience sample of 100 participants will be recruited.

Patients meeting eligibility criteria are randomly assigned to the intervention MedDiet + (*n* = 50) or control (*n* = 50) groups through an online block randomisation generator. Due to the nature of the trial, the participants and the registered dietitians responsible for implementing the study are not blinded. However, the clinicians evaluating the clinical outcome measures and the researchers performing the laboratory tests are blinded.

#### Primary endpoint

Change of DAS28-ESR (Disease Activity Score in 28 joints calculated with erythrocyte sedimentation rate) from baseline to 12 Weeks.

#### Secondary endpoints

Proportion of patients achieving:◦ European Alliance of Associations for Rheumatology (EULAR) moderate or good response◦ DAS28-ESR < 2.6Change in DAS28-CRP (Disease Activity Score in 28 joints calculated with C-reactive protein)Change on ultrasound score (32 joints scored 0-3 for grey scale and power Doppler)Proportion of patients who had a 10% improvement in ultrasound scoreChange in Short Form 36 Health Survey Questionnaire (SF36) resultsChange in Health Assessment Questionnaire (HAQ) resultsChanges in α- and β- diversity of the gut and oral microbiotaChanges in the relative abundance of *Lactobacillus/Limosilactobacillus* and* Bifidobacterium* species in the gutChanges in butyrate-producing species in the gut microbiotaChanges in H2S-producing species in the gut microbiotaChange in the lactulose/mannitol ratioChange in Endotoxemia measured by TLR4 activation in reporter cellsChange in inflammatory biomarkers (C-Reactive Protein, CPR; Erythrocyte sedimentation rate, ESR, faecal calprotectin)Change in serum soluble CD14 (CD14s), lipopolysaccharide-binding protein (LBP), and intestinal fatty acid binding protein levels (IFABP)Change in lipid profile (Triglycerides, Total Cholesterol, HDL and LDL Cholesterol)Change in body composition (Fat Mass, Fat-Free Mass, Total Body Water and Body Cell Mass)Change in anthropometric measurements (body mass index, BMI, and waist circumference)

We will also analyse zonulin levels, serum proteomics, and serum glycomics.

### Recruitment and eligibility criteria

RA patients diagnosed according to the ACR/EULAR2010 criteria [23], aged 18 years old or older, are invited to participate in this study if eligibility criteria are met at their regular follow-up RA consultations. All participants sign a written informed consent form before any study procedures. Our inclusion criteria are diagnosis duration of at least one year, active disease (DAS28-ESR ≥ 2.6 units), stable medication for at least 12 weeks prior to the baseline assessment (including intra-articular steroid injections), and a low or medium adherence to the MedDiet (defined as a score of < 10 points in the 14-item tool by the PREvención com DIeta MEDiterránea trial, PREDIMED). Patients requiring therapeutic adjustments and/or intra-articular steroid injections during the trial are excluded. Our exclusion criteria are: antibiotic therapy within 4 weeks before enrolment; prednisolone dose > 7.5 mg/day; persistent use of non-steroidal anti-inflammatory drugs: diagnosis of inflammatory or irritable bowel disease, celiac disease, chronic diarrhoea; diagnosis of other immune-mediated or inflammatory diseases; major organ dysfunction; cancer diagnosed in the last five years; presence of health conditions which may impair the ability to consent to study participation (cognitive impairment/psychiatric disease). Regarding the use of antibiotics, although a general recommendation for a washout period is challenging to define, according to literature, a minimum of 4 weeks since cessation of antibiotics is recommended [24] and is considered in this trial. The overall diagram flow of the study is shown in the SPIRIT figure illustrated in Fig. 1. The SPIRIT checklist is provided as supplementary material.

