### Interventions and comparators

#### MedDiet + group

The intervention is carried out for 12 weeks at ULS Santa Maria and includes an educational-based nutritional intervention with a structured nutrition plan prescribed by registered dietitians, educational food baskets, educational digital content, and clinical culinary workshops.

At baseline, a personalised nutritional plan is elaborated for each participant, and its implementation is closely monitored through weekly follow-up calls and monthly face-to-face appointments to fully involve participants and minimise dropout rates. To define an adjusted nutritional plan, nutritional requirements are individually assessed considering the patients' nutritional status and physical activity level. Energy, as well as protein, carbohydrate, and lipid requirements are calculated in agreement with the European Food Safety Authority (EFSA) dietary reference values [25]. The nutritional plan includes the number of food portions of each food group that participants must consume, in agreement with the MedDiet recommendations for the adult population [26]. To complement the traditional MedDiet, additional advice is provided to promote the consumption of specific fermented foods that potentially contain probiotic microorganisms, vitamins and bioactive compounds, such as fermented beverages, including kefir (provided for daily consumption) and kombucha (provided for consumption 2x/week). Foods with anti-inflammatory properties are also recommended, including sources of n-3 polyunsaturated fatty acids (PUFAs), such as oily fish, nuts and seeds, and a high amount of extra-virgin olive oil. The intake of vitamins, carotenoids, and phenolic compounds is promoted by the consumption of a wide variety of fruits, vegetables, legumes, whole grains, nuts and seeds, tea and infusions, herbs and spices, and extra-virgin olive oil. The nutritional plan can be adjusted if patients report issues with the consumption of specific foods.

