**Fig. 2 Fig2:**
[figure not shown]
– Overview of the data collection throughout the trial. Visual representation of the specific variables to be collected in each phase of the study, which are identical at baseline and at the end of the trial (12th week) for both groups. Only the intervention group (MedDiet +) has in-person follow-up consultations with nutritional assessment at 4th and 8th weeks. *Sociodemographic and lifestyle data are also collected at baseline. Abbreviations: CRP: C-reactive protein; DAS28: Disease Activity Score using 28 joint counts; ESR: Erythrocyte sedimentation rate; HAQ: Health Assessment Questionnaire; I-FABP: Intestinal-fatty acid binding protein; LPS: Lipopolysaccharides; PREDIMED: Prevención con Dieta Mediterránea; SF36: 36-Item Short Form Health Survey

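### Patients who need a therapy change or joint injection during the trial are excluded after randomisation, on an event related to the primary endpoint, and nothing keeps them in the comparison

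*Protocol article*

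**What the plan says.** All references are to the protocol article.

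- Recruitment and eligibility criteria: "Patients requiring therapeutic adjustments and/or intra-articular steroid injections during the trial are excluded". The same paragraph has a separate criterion for the period before entry: "stable medication for at least 12 weeks prior to the baseline assessment".
- Study design, setting and aims: "Patients meeting eligibility criteria are randomly assigned to the intervention" or control group, 50 per arm. Participants and dietitians are unblinded; clinical assessors and laboratory staff are blinded. On size, "a convenience sample of 100 participants will be recruited", and the unknown effect is described as "making it unfeasible to conduct a formal sample size calculation".
- Primary endpoint: "Change of DAS28-ESR (Disease Activity Score in 28 joints calculated with erythrocyte sedimentation rate) from baseline to 12 Weeks". The secondary endpoints include the proportions with EULAR response and with DAS28-ESR below 2.6.
- MedDiet + group: the nutritional plan is "closely monitored through weekly follow-up calls and monthly face-to-face appointments". The Fig. 2 legend adds: "Only the intervention group (MedDiet +) has in-person follow-up consultations with nutritional assessment at 4th and 8th weeks". Controls receive a flyer at baseline.
- Clinical outcome measures: clinical assessment takes place at baseline and week 12 in both arms.
- Data management and statistical analysis: t-tests or non-parametric equivalents, regression, ANCOVA and MANCOVA. The section does not say that patients who meet the exclusion are followed or analysed.

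**The concern.** Stability before baseline has its own criterion and only eligible patients are randomised, so an event during the trial falls after assignment. In patients with active disease on stable medication, needing a therapy change or a joint injection tends to go with worsening joints, which is what DAS28-ESR measures. Removing such patients selects on something close to the outcome. Adjusting for baseline covariates does not undo that.

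Two things are at stake. If the diet works partly by preventing flares, more controls than intervention patients are removed and the estimated benefit shrinks. And if non-responders leave the denominator, the responder proportions look better than they are in the randomised groups.

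**Working it through.** **Plan's own figure.** There is none to reproduce: no SD, effect size, power or expected exclusion rate is stated. Every input below except n = 50 per arm is an assumption.

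**Model.** Change in DAS28-ESR is normal with mean μ and SD σ. A patient whose change exceeds a cut-off c is excluded with probability p. With a = (c − μ)/σ, q = 1 − Φ(a) and φ the standard normal density:

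- share excluded = p·q
- mean of those kept = μ − p·σ·φ(a)/(1 − p·q)

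Inputs: σ = 1.1, c = +0.6, control mean −0.2, intervention mean −0.7 (true difference −0.50).

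- Control: a = 0.8/1.1 = 0.727, q = 0.2335, φ = 0.3062
- Intervention: a = 1.3/1.1 = 1.182, q = 0.1186, φ = 0.1984

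**Same rule in both arms, true difference −0.50**

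| p | Excluded, intervention | Excluded, control | Mean kept, intervention | Mean kept, control | Difference |
|---|---|---|---|---|---|
| 0.5 | 5.9% | 11.7% | −0.816 | −0.391 | −0.425 |
| 0.7 | 8.3% | 16.3% | −0.867 | −0.482 | −0.385 |

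**Same rule in both arms, no true effect.** Both arms shift equally, so the difference stays at 0. A separate simulation (50 per arm, 20,000 replicates, SD 1.0 or 1.2, control mean 0, cut-off 0.6 or 1.2, p of 0.5 or 1) gave a type I error of about 0.05.

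**Same rule, true benefit 0.6, same simulation.** The estimate falls to 0.33–0.54. Power falls from 0.84–0.85 to 0.54–0.79 at SD 1.0, and from about 0.70 to 0.36–0.61 at SD 1.2.

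**Exclusion that differs by arm, no true effect (both means −0.2)**

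- p = 0.7 against 0.3: −0.482 − (−0.309) = −0.173, favouring the arm with more exclusions. Swapping the arms gives +0.173.
- p = 0.5 against 0.2: −0.391 − (−0.271) = −0.120.

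**Responder denominators (illustration).** 15 responders of 50 is 30%. If eight non-responders leave, 15 of 42 is 36%.

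**What an as-randomised analysis would return.** Suppose a therapy change lowers DAS28-ESR by e = 1.0 to 1.2 (assumed). The expected difference is −0.50 + e·p·(0.2335 − 0.1186):

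- p = 0.5: −0.443 (e = 1.0) to −0.431 (e = 1.2)
- p = 0.7: −0.420 (e = 1.0) to −0.403 (e = 1.2)

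**The case against.** **The sentence may not concern the analysis.** It stands among the eligibility criteria and does not say that patients are dropped from analysis; it could mean withdrawal from study procedures. Analysis sets are often left to a full protocol or SAP, which is not shown. This holds as far as the wording goes. But withdrawal would also lose the week-12 value, and an SAP that analysed everyone would have to depart from the stated rule.

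**Unequal detection.** A reader might infer that the rule will be triggered more often in MedDiet + because contact is denser there, and so that a false benefit is to be expected. The article does not support that. The extra contact is dietetic, clinical assessment has the same schedule in both arms, outcome assessors are blinded, and no passage gives dietitians a part in therapy changes. Unblinded participants and denser contact make unequal exclusion possible, no more. The 70/30 and 50/20 splits have no source.

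**Worst outcomes.** A reader might also infer that precisely the worst outcomes are removed. Adjustments are not limited to escalation, so this is only a tendency, and 12 weeks of stable medication at entry may make changes uncommon.

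**Size.** The distortions in the SD 1.1 model (0.075 to 0.115 of attenuation, 0.120 to 0.173 spurious) are below one standard error of the difference, 1.1·√(2/50) = 0.22. That is true, but they are systematic, and the power loss in the wider scenarios is not trivial.

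**The remedy.** If a therapy change itself lowers DAS28-ESR, the as-randomised contrast is attenuated about as much as the exclusion analysis. This stands, and limits what the fix can be said to achieve.

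**Conclusion.** The point holds: the article states a post-randomisation exclusion on an event related to the primary endpoint, and no passage keeps these patients in the comparison. Followed as written, it means that the analysed arms are not the randomised groups, whether excluded means withdrawn or dropped at analysis.

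Under the assumed inputs, equal exclusion in both arms reduces a true difference of −0.50 to between −0.425 and −0.385, and responder proportions are inflated. With equal exclusion and no true effect there is no bias. A spurious difference of about 0.12 to 0.17, in either direction, arises only if exclusion differs by arm. The actual size cannot be known from the article.

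**What to change.** 1. Limit the sentence to eligibility before randomisation.
2. Collect week-12 DAS28-ESR on every randomised participant. As the primary analysis, compare assigned arms regardless of therapy changes (treatment policy).
3. For the responder endpoints, keep everyone in the denominator and count participants with escalated therapy or an injection as non-responders.
4. Record therapy changes and injections in both arms from the same hospital records, which the article already uses for medication history.
5. Keep the exclusion analysis only as a labelled sensitivity analysis.
6. For patients already excluded, recover week-12 values where they exist. Otherwise use a sensitivity analysis that assumes outcomes worse than those of completers. DAS28-ESR is measured only at baseline and week 12, so imputation from baseline alone would largely reproduce the completers' result.

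The cost is a wording change and week-12 data on some further patients. The downside is that the as-randomised contrast includes the effect of therapy changes and may itself be attenuated. It restores a valid randomised comparison and sound denominators, not the effect of diet alone. Patient care does not change.

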**Fig. 1 Fig1:**
[figure not shown]
SPIRIT figure with standard protocol items of the TASTY trial. The SPRIT figure illustrates key components of the TASTY trial protocol and data collection time points from enrolment to the end of the 12 weeks. Abbreviations: Lipopolysaccharides (LPS). *Only in the MedDiet + Group

### Interventions and comparators

#### MedDiet + group

The intervention is carried out for 12 weeks at ULS Santa Maria and includes an educational-based nutritional intervention with a structured nutrition plan prescribed by registered dietitians, educational food baskets, educational digital content, and clinical culinary workshops.

At baseline, a personalised nutritional plan is elaborated for each participant, and its implementation is closely monitored through weekly follow-up calls and monthly face-to-face appointments to fully involve participants and minimise dropout rates. To define an adjusted nutritional plan, nutritional requirements are individually assessed considering the patients' nutritional status and physical activity level. Energy, as well as protein, carbohydrate, and lipid requirements are calculated in agreement with the European Food Safety Authority (EFSA) dietary reference values [25]. The nutritional plan includes the number of food portions of each food group that participants must consume, in agreement with the MedDiet recommendations for the adult population [26]. To complement the traditional MedDiet, additional advice is provided to promote the consumption of specific fermented foods that potentially contain probiotic microorganisms, vitamins and bioactive compounds, such as fermented beverages, including kefir (provided for daily consumption) and kombucha (provided for consumption 2x/week). Foods with anti-inflammatory properties are also recommended, including sources of n-3 polyunsaturated fatty acids (PUFAs), such as oily fish, nuts and seeds, and a high amount of extra-virgin olive oil. The intake of vitamins, carotenoids, and phenolic compounds is promoted by the consumption of a wide variety of fruits, vegetables, legumes, whole grains, nuts and seeds, tea and infusions, herbs and spices, and extra-virgin olive oil. The nutritional plan can be adjusted if patients report issues with the consumption of specific foods.

Educational food baskets are delivered weekly with different typical ingredients of the MedDiet + pattern to encourage their inclusion in the patients' daily meals. This strategy ensures that every participant receives the same resources to meet the nutritional recommendations. We have secured a partnership agreement with a supermarket chain to overtake logistic aspects. Ingredients such as extra virgin olive oil, whole grains (whole grain bread, rice and pasta, oats), fresh fruits and vegetables, legumes, nuts and seeds, canned sardines and mackerels, herbs and spices, plain yoghurt, kefir, and kombucha are being provided.

Educational content consists of video recordings and two recipe books to share new ideas for cooking recipes, as well as educational and useful content to help participants meet the nutritional recommendations. It intends to empower patients with knowledge of different dishes and cooking methods to promote the inclusion of the foods provided in the food baskets. Recipes for other fermented foods, such as sauerkraut and sourdough bread are also included in the educational content. Finally, access to an online clinical culinary workshop is provided. The clinical culinary workshop allows for the application of the provided nutritional knowledge into culinary preparations through the demonstration of recipes and culinary methods.

